# Physical micro-environment interventions for healthier eating in the workplace: protocol for a stepped wedge randomised controlled pilot trial

**DOI:** 10.1186/s40814-017-0141-z

**Published:** 2017-06-09

**Keywords:** Physical micro-environment interventions, Choice architecture, Nudging, Stepped wedge trial, Randomised controlled trial, Healthier eating, Workplace interventions, Size, Availability, Labelling

## Abstract

**Background:**

An estimated one third of energy is consumed in the workplace. The workplace is therefore an important context in which to reduce energy consumption to tackle the high rates of overweight and obesity in the general population. Altering environmental cues for food selection and consumption—physical micro-environment or ‘choice architecture’ interventions—has the potential to reduce energy intake. The first aim of this pilot trial is to estimate the potential impact upon energy purchased of three such environmental cues (size of portions, packages and tableware; availability of healthier vs. less healthy options; and energy labelling) in workplace cafeterias. A second aim of this pilot trial is to examine the feasibility of recruiting eligible worksites, and identify barriers to the feasibility and acceptability of implementing the interventions in preparation for a larger trial.

**Methods:**

Eighteen worksite cafeterias in England will be assigned to one of three intervention groups to assess the impact on energy purchased of altering (a) portion, package and tableware size (*n* = 6); (b) availability of healthier options (*n* = 6); and (c) energy (calorie) labelling (*n* = 6). Using a stepped wedge design, sites will implement allocated interventions at different time periods, as randomised.

**Discussion:**

This pilot trial will examine the feasibility of recruiting eligible worksites, and the feasibility and acceptability of implementing the interventions in preparation for a larger trial. In addition, a series of linear mixed models will be used to estimate the impact of each intervention on total energy (calories) purchased per time frame of analysis (daily or weekly) controlling for the total sales/transactions adjusted for calendar time and with random effects for worksite. These analyses will allow an estimate of an effect size of each of the three proposed interventions, which will form the basis of the sample size calculations necessary for a larger trial.

**Trial registration:**

ISRCTN52923504

## Background

Reducing excess consumption of food and drink is core to tackling the high prevalence of overweight and obesity in the population [1]. It is estimated that about one third of our daily energy intake is consumed while at work [2], with the majority of food consumed not brought from home [3]. The National Institute for Health and Care Excellence (NICE) estimates that a company employing 1000 people could lose more than £126,000 a year in reduced productivity solely due to obesity [4]. Whilst a systematic review is underway [5], there is currently limited evidence of the impact of interventions within workplaces to improve employees’ diets.

In a recent review that included six studies examining dietary interventions in the workplace, four reported small increases in fruit and vegetable consumption following implementation of a range of interventions [6]. However, outcomes were mainly based on self-report and incomplete reporting of all the studies made judgements of risk of bias unclear. In addition, the range of interventions assessed was based largely on providing information (with most studies implementing different kinds of nutritional education campaigns via posters, leaflets, and group workshops delivered at workplaces), commonly regarded as insufficient to tackle obesity [7]. Evidence is now accumulating to suggest that altering cues in small-scale or micro physical environments may provide a more effective way of changing behaviour, often without awareness and in ways that do not place demands on our limited cognitive resources [8, 9]. This is sometimes referred to as ‘nudging’ or ‘choice architecture’ [10]. In keeping with this, a recent report on obesity identified the potential value of a number of such choice architecture interventions [7].

We propose a pilot study to estimate the potential impact of three sets of physical micro-environment interventions to reduce energy purchased in workplace cafeterias in preparation for a future larger trial. A further aim is to examine the feasibility of recruiting eligible worksites, and identify barriers to the feasibility and acceptability of implementing the interventions in preparation for a larger trial.

### Portion, package and tableware size

One promising target for interventions in physical micro-environments is the size of food portions, their packages and the tableware used to consume them. The most robust review to date of the impact of portion, package and tableware size upon consumption [11, 12], suggests that the scale of the ‘portion size effect’ (describing the observation that people consistently consume more when offered larger portions, packages or tableware) is such that, removing larger portions, packages and tableware from the diet could reduce the daily energy intake of UK adults by up to 16% (279 calories).

### Availability of healthier vs. less healthy foods

A second intervention is to alter the availability of foods and drinks by increasing the range of healthier foods/drink options and/or decreasing the range of less healthy options. A recent review of interventions in vending machines found that sales of healthier items were increased in five of the six identified studies that increased their availability, with no loss of overall sales volume [13]. Indeed, availability and portion size together represent two of the top three interventions suggested in the McKinsey Global Institute report [7] as having the highest likely impact across the population. A Cochrane review of the impact of availability interventions in all settings is currently underway [14].

### Energy labelling

A third intervention that can be used in workplace settings is to provide labels displaying energy (calorie) content. Recent review evidence shows that calorie labelling at point of consumption can reduce average daily energy intake from food and drinks [15].

However, recent Cochrane reviews of the three interventions used in this pilot study (11, 14, 15) have not identified any randomised studies in worksite cafeterias. Prior to designing and conducting a larger trial, several key design uncertainties need to be addressed. These include the feasibility of recruiting eligible worksites, the suitability of workplaces for implementing one of the three interventions, the practicalities associated with implementing the interventions including any challenges with implementation or acceptability, and worksites’ ability to provide the required data and comply with the study protocol. The pilot study will also enable us to estimate required sample sizes needed for a larger trial, by providing estimates of likely effect sizes for each of the three interventions and identifying key characteristics and issues with the data that are likely to be encountered.

We propose to pilot three types of interventions with the potential to reduce the energy from food and drink purchased in workplace cafeterias:i.reducing the size of portions, packages and tableware;ii.increasing the availability of lower energy (calorie) foods and drinks, relative to higher energy foods and drinks;iii.labelling foods and drinks with their energy (calorie) content.

In particular, we will examine:The impact upon the total energy (calories) of food and drink purchased in workplace cafeterias of:smaller portions and packages of foods and drinks, and smaller tableware;removing some of the higher energy items available and replacing these with lower energy options;providing energy (calorie) labels on foods and drinks.The extent to which the impact of the interventions varies with the socio-demographic profiles of the participating workplaces.

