## Methods

### Study design

A stepped wedge design [16] (see Fig. 4) was selected, due to being simpler to implement and better able to capture intervention effects than parallel cluster randomised or multiple-treatment reversal (ABAB) designs. Stepped wedge trials are a type of RCT which involve sequential, but random rollout of an intervention over multiple time periods. Stepped wedge trials typically have a baseline period in which observations are made while all participating sites are unexposed to the intervention, and one time period in which all participating sites are exposed to the intervention (at the end of the trial) [16]. As such, this design allows examination of changes in purchasing within each worksite cafeteria depending on the time-period (baseline vs. intervention); as well as differences in purchasing between worksite cafeterias at different time-points of the stepped wedge trial. Each intervention will be evaluated singly, in one of three sets of six worksites. The 18 worksite cafeterias (one cafeteria per worksite) will be allocated to one of these three sets depending on their readiness to start, determined by data collection systems in place. The first six sites to be ready will be allocated to the first intervention ready for implementation: labelling. The remaining 12 sites will be randomly allocated to implement either the size or the availability interventions. The unit of analyses is the worksite cafeteria, not the individuals using the worksite cafeteria (see Fig. 4).

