**Fig. 4 Fig4:**
[figure not shown]
A graphical presentation of the stepped wedge design used for each intervention in the study

Within each of the three sets of six worksite cafeterias, the time at which the intervention is introduced will be randomly determined to control for time trends while maximising sample size. Worksite cafeterias will be allocated to a phase of the stepped wedge design by means of random permutations using random variates of the uniform distribution [17]. The randomisation will be performed by a statistician, with the assistance of computer software.

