### Sample

Eighteen English worksite cafeterias recruited from companies that are members of the Institute for Grocery Distribution (IGD; comprising 1027 members), selected on the basis of:Number of employees (>350)Mix of office-based and other site types (to recruit sites that are likely to represent different ranges of socio-economic status)Ability to provide weekly data on sales of individual items and their energy content

Worksites from any region within England would be eligible. Managers of identified eligible worksites will be contacted, and given details on the design of the pilot trial, as well as all the requirements regarding participation in the pilot trial, including the range of possible timings for implementing the intervention in the stepped wedge design. Please see Fig. 5 for a CONSORT flow diagram delineating the flow of participating sites through the pilot trial.

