#### Other measures

Various other measures will be collected that will allow us to estimate the primary and secondary outcomes with greater precision. Covariates examined for all three interventions include: worksite demographic characteristics (age, gender, and dominant occupational status); day of week (if the distribution of the data allows for analysis per day); and weather conditions.

The following will also be recorded for each of the three interventions:i)Size: mean energy (calorie) per product pre-intervention; mean reduction (%) in energy (calorie) per product; mean price pre-intervention; mean reduction (%) in price; mean size of tableware pre-intervention; mean reduction (%) in size of tableware.ii)Availability: proportion of food/drink intervention items that are healthier pre-intervention; proportion of food/drink items that are targeted in the intervention; mean energy (calories) per item pre-intervention; reduction (%) in proportion of intervention items that are healthier from pre-intervention; reduction (%) in energy (calories) per item from pre-intervention; Mean price pre-intervention; mean change (%) in price.iii)Labelling: mean energy (calories) per item pre-intervention; mean energy (calories) per item during intervention.

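### The aim to examine how impact varies with workplace profile is not protected by the allocation: the site-type mix is sought across all 18 sites, and no stratification is stated when they are divided into sets of six

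*Protocol article*

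**What the plan says.** The end of the Background (under Energy labelling) lists what the pilot will examine. Besides the impact of each intervention on energy purchased, it names "The extent to which the impact of the interventions varies with the socio-demographic profiles of the participating workplaces".

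The Sample section makes site type a selection criterion for the 18 cafeterias: "Mix of office-based and other site types (to recruit sites that are likely to represent different ranges of socio-economic status". The criterion applies to the whole sample and not to each set.

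The Study design section then divides the sites. "Each intervention will be evaluated singly, in one of three sets of six worksites". For labelling, "The first six sites to be ready will be allocated to the first intervention ready for implementation: labelling"; readiness depends on the data collection systems in place. For the others, "The remaining 12 sites will be randomly allocated to implement either the size or the availability interventions". No stratification or balancing on site type is stated at either point.

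Other measures lists worksite age, gender and dominant occupational status as covariates, among measures that will "allow us to estimate the primary and secondary outcomes with greater precision". Intervention impact analyses fits a separate linear mixed model for each intervention.

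**The concern.** The objective is one of effect modification: does the same intervention work differently at sites with different profiles? With one intervention per set and one model per intervention, the only comparison free of differences between interventions is among the six sites of a set. If all six are of one type, that set says nothing about variation by type. The remaining route would compare sets, and sets differ in intervention and, for labelling, in readiness as well.

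The protocol recruits for a range of socio-economic status but states no step that carries the range into each set. An analysis plan can add an interaction term later. It cannot restore a contrast that the allocation has removed. What is at stake is a stated objective of the pilot, not its primary outcome or its feasibility aims.

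**Working it through.** The protocol gives no figure of its own to reproduce here, beyond 3 sets × 6 sites = 18.

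**Inputs from the protocol article.** 18 sites; six to labelling by readiness; 12 split at random, taken as 6 and 6 (Study design). A 4-week baseline, then six two-weekly steps (Procedure).

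**Assumed.** K, the number of minority-type sites among the 12. It is not stated, so K = 2 to 6 is shown.

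**1. Chance that a randomised set has no contrast.** There are C(12,6) = 924 equally likely splits. All K minority sites fall in one set with probability 2 × C(12−K, 6−K) / 924, which leaves the other set without that type:

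- K = 2: 2 × C(10,4) / 924 = 420/924 = 45%
- K = 3: 2 × C(9,3) / 924 = 168/924 = 18%
- K = 4: 2 × C(8,2) / 924 = 56/924 = 6%
- K = 5: 2 × C(7,1) / 924 = 14/924 = 1.5%
- K = 6: 2 × C(6,0) / 924 = 2/924 = 0.2%

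**2. Chance of little contrast.** A set with at most one site of a type rests the comparison on a single site. The chance that at least one of the two sets is in that position is one minus the chance that both hold at least two of each type:

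- K = 2 or 3: 100% (there are too few to give each set two)
- K = 4: 1 − C(4,2) × C(8,4) / 924 = 1 − 420/924 = 55%
- K = 5: 1 − 2 × C(5,2) × C(7,4) / 924 = 1 − 700/924 = 24%
- K = 6: 1 − (2 × C(6,2) × C(6,4) + C(6,3) × C(6,3)) / 924 = 1 − 850/924 = 8%

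**3. All three sets.** Readiness has no known probability. Treating it as random, purely for illustration, the chance that at least one of the three sets has no contrast is 74%, 47%, 15% and 2.5% for 3, 4, 6 and 9 minority-type sites among the 18.

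**4. What the loss does to the estimate.** I used generalised least squares for six sites, one per step, over 16 weeks (4 + 6 × 2). Assumptions: a constant intervention effect, and exchangeable within-site correlation of 0.5 to 0.95.

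- One type only: the model with site type and its interaction has rank 17 for 19 parameters, so the interaction cannot be estimated.
- 1 site against 5: the interaction standard error is about 1.6 to 2.3 times that of the intervention effect.
- 3 against 3: about 1.25 to 1.4 times.

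**5. After stratifying the 12 by site type.** With K of 2 or more, each set receives at least one minority site, so the probabilities in step 1 become 0. With K = 4 each set receives two.

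**The case against.** **Silence is not refusal.** The article says that the 12 sites are randomly allocated but not how, and a condensed article may leave stratification or an interaction model to a fuller document. For the interaction model this stands, and its absence is not part of the point. For the allocation it stands in part: stratification may exist elsewhere. But the article does fix that labelling is filled by readiness and that the mix is sought over the whole sample.

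**The profile is more than office against other.** The article measures it by age, gender and dominant occupational status. This stands. Age and gender composition will probably differ among any six sites, so total loss of contrast concerns categorical variables only.

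**The risk may be small.** This also stands. With a near-even mix, the chance of total loss is 1.5% or less among the 12.

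**It is a pilot.** The abstract names effect-size estimation and feasibility as the aims, and the Discussion calls the effect estimates exploratory. With six sites, no allocation makes a between-site modifier precise. This argues for a modest claim. It does not argue for leaving the contrast to chance when protecting it costs little.

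A reader might also infer three stronger points that the documents do not support:

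- *Profile enters only as a precision covariate.* Other measures gives precision as a purpose, but it neither limits the covariates to main effects nor excludes an interaction.
- *Readiness tracks site type.* Nothing in the article says so, and the Sample section requires every site to be able to supply weekly item-level data.
- *A set with one type early and the other late cannot separate profile from season.* Steps are assigned "by means of random permutations using random variates of the uniform distribution", with no restriction stated, so such an order can occur. But the model adjusts for calendar time. Under the assumptions of step 4, a fully segregated 3/3 order has full rank (19 of 19), with an interaction standard error only 7 to 8% above the best order. Requiring an early and a late start for each type would not reliably help. With two minority sites and correlation 0.5, it would allow steps 1 and 6 (standard error 0.383) and forbid steps 1 and 2 (0.363), with residual plus site variance set to 1. Only an effect that changes with length of exposure would stay mixed with type.

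**Conclusion.** The point holds for the composition of the sets. The protocol commits to examining variation in impact by workplace profile, evaluates each intervention in six sites, and states nothing that secures a mix of site types within a set. For a categorical profile, the chance that one of the two randomised sets lacks the minority type runs from 45% to 0.2% as the assumed number of such sites among the 12 rises from 2 to 6. The real figure depends on a count that the article does not give. For the labelling set no probability can be attached, because readiness is not random. Step order is not a defect on this ground. The consequence is limited to one secondary objective, which may go unanswered for one or more interventions.

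**What to change.** Stratify the random split of the 12 sites between size and availability by site type (office against other), which the Sample section already uses for selection. If a stratum has an odd number of sites, let chance decide which set receives the extra one, and keep six sites per set.

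Describe the objective on socio-demographic profile as exploratory. State that no site-type contrast will be reported for any set that holds only one type. This applies equally to the labelling set, whose make-up is decided by readiness and which stratifying the other 12 does not change. Leave the random step order as it is.

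The cost is a slightly more constrained randomisation and a more modest claim. No new data are needed, but the stratification must be in place before the 12 sites are randomised.

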### Interventions

These will take place in worksite cafeterias. The precise nature of the interventions will vary between sites, depending upon the food, drink and tableware currently available. For example, if sugar-sweetened beverages are already those at the smallest available size (e.g. a 150 ml can or carton of drink) these will not be a focus for reduction in size. The target products for each intervention will be documented and included as covariates in the analyses.

In particular, for the size intervention we propose to intervene on all products sold in the workplace cafeterias for which the energy content can be meaningfully reduced. We will therefore exclude from the size intervention products containing little or no energy (<5 kcal/100 g), such as water or chewing gum, and all fresh fruit and vegetables with no added fat or sugar. For the availability intervention, we propose using predominantly energy-based cut-offs to define ‘healthier’ vs. ‘less healthy’ options (more details are provided below under the availability intervention description). For the labelling intervention, we propose to intervene on all products sold in the workplace regardless of macronutrient profile (with the exception of items made individually by the workplace patrons for which the energy content of individually made items cannot be determined beforehand, for example for foods offered on a salad or a wok bar). For all three interventions, hot drinks will also be excluded, due to difficulties with recording the sales data for these products across worksites.i.SizeResearch questionWhat is the impact on energy purchased of reducing the size of portions and/or packages of foods and drinks and/or tableware size in worksite cafeterias?The intervention will be applied across a combination of the following:
*Portion sizes of served foods*: reduce the size of portions of higher energy food and drink items served in worksite cafeterias by approximately 10% to 15%, includingMain meals (e.g. lasagne)Sides (e.g. chips or fries)Desserts, cakes, cookies and biscuits
This might involve producing 16 portions of lasagne from a tray that was previously cut into 14 portions, or 14 slices of cake from a cake that was previously cut into 12 slices.
*Pre-packaged products*: replace currently available packaged food and drinks in cafeterias with the next smaller available package size (see Fig. 1 for an example).

**Fig. 1 Fig1:**
[figure not shown]
An example of intervening on the size of packaged products (e.g. replacing a 500 ml bottle with a 375 ml bottle or 330 ml bottle or can)
*Tableware*: the size of available glasses, plates, bowls and/or cutlery used to serve and consume food and drink items will be reduced to the next smaller available size. For example, a plate 30 cm in diameter may be replaced by a plate 27 cm in diameter.
For all sites, the standard retail price of the packages and portions will be used. In the case of reducing portion size of items which are not pre-packaged (such as main meals or cakes), prices will be reduced proportionally.ii.AvailabilityResearch questionWhat is the impact on energy purchased of reducing the number of less healthy foods and drinks available in worksite cafeterias and replacing these with the equivalent number of healthier food and drinks?This intervention will involve keeping constant the number of options offered but altering the ratio of healthier to less healthy options by reducing the less healthy foods and drinks (products or units of the same product) available and increasing the healthier foods and drinks available (see Fig. 2 for an example).

